## Abstract

**Background:**

A high intake of salt is a major risk factor for cardiovascular diseases. Despite decades of effort to reduce salt consumption, the salt intake in China is still considerably above the recommended level. Thus, this study aims to design and implement an intelligent household added salt monitoring system (SALTCHECKER) to monitor and control added salt consumption in Chinese households.

**Methods:**

A randomized controlled trial will be conducted among households to test the effect of a SALTCHECKER in Chongqing, China. The test modalities are the SALTCHECKER (with a smart salt checker and a salt-limiting WeChat mini programme) compared to a salt checker (with only a weighing function). The effectiveness of the system will be investigated by assessing the daily added salt intake of each household member and the salt consumption-related knowledge, attitude and practice (KAP) of the household’s main cook. Assessments will be performed at baseline and at 3 and 6 months.

**Discussion:**

This study will be the first to explore the effect of the household added salt monitoring system on the reduction in salt intake in households. If the intelligent monitoring system is found to be effective in limiting household added salt consumption, it could provide scientific evidence on reducing salt consumption and preventing salt-related chronic diseases.

**Trial registration:**

Chinese clinical trial registry (Primary registry in the World Health Organization registry network): ChiCTR1800018586. Date of registration: September 25, 2018.

## Background

Excessive dietary intake of sodium is associated with the increasing risk of hypertension and cardiovascular diseases [1]. The current average salt intake in Chinese adults (10.4 ± 0.2 g/d) is higher than the recommended level of the World Health Organization (5 g/d) and that of the Chinese Nutrition Society (6 g/d) [1–3]. In China, most dietary sodium intake is from salt added in home cooking [4, 5]. Therefore, innovative interventions to reduce salt intake at the household level should be a priority in China.

Several salt reduction programmes have been carried out around the world and are considered to be effective [6–9]. Programmes in developed countries have achieved excellent results; they promote food nutrition labels, educate the public, strengthen cooperation with food companies and reduce salt content in processed foods [10–13]. In China, evidence-based strategies to reduce salt intake are available [14–19]. The common salt reduction initiatives are salt substitutes, salt-restricting tools and health education [20]. However, the implementation of these strategies is limited [10, 14–19], mostly due to the high price of salt substitutes [20], inappropriate belief in salt-using experience and lack of awareness about the harms of excessive salt intake in residents, and the complex operation of the salt-limiting spoon [21].

Increasing salt-related knowledge levels and favourable attitudes are beneficial to improve salt-limiting behaviours. The knowledge of salt use and its impact on health is limited among residents in China [22]. In an earlier study in China, favourable actions of dietary sodium reduction were more likely to occur among those who were aware of the link between sodium and hypertension, and less likely to occur among those who had unfavourable attitudes toward dietary sodium reduction [7]. Therefore, evaluating the salt consumption-related knowledge, attitude and practice (KAP) is essential to initiate salt-limiting nutritional education and promote healthy salt behaviour.

Currently, the main methods to monitor salt intake include 24-hour urine collection, spot urine collection and dietary surveys [23]. However, these methods have some shortcomings. Although, the 24-hour urine collection is reliable for evaluating salt intake [24], the laborious collection and detection of urine samples and the lack of a suitable method for correctly identifying incomplete samples were reported as potential barriers [25]. Spot urine sampling is a convenient and affordable alternative to estimate 24-hour urinary sodium excretion, but has the disadvantages of difficult selection of the time of spot urine sampling monitoring, and non-representative and unsuitable spot urine sampling for individual assessment [25, 26]. Dietary recalls and weighed diet records are time-consuming and labour-intensive and often underestimate actual salt intake [25]. Therefore, an accurate and convenient method to assess the salt intake of individuals is needed.

The Internet of Things (IOT) is the network of physical devices, vehicles, home appliances and other items embedded with electronics, software, sensors, actuators and connectivity, which enable these things to connect, collect and exchange data [27]. Currently, IOT technology is cumulatively applied in health education and promotion, such as physical activity recognition and monitoring [28], personal health records [29], smart care for specific populations [30–32] and risk prediction [33]. However, IOT technology has not yet been applied to monitor added salt consumption. WeChat, a social media platform, similar to Facebook, widely used in China [34], has great potential to be integrated with IOT technology for salt reduction intervention. A WeChat mini programme appears to be similar to general apps, however, there is no need to install or uninstall them on the smartphone; this feature improves accessibility and convenience [35]. This study will combine IOT technology, a WeChat mini programme and a salt-limitation intervention to provide an innovative idea and approach for the monitoring and reduction of household salt intake.

In recent years, studies in the real-world settings have become increasingly important in providing evidence of treatment effectiveness in clinical practice [36]. Real-world research is made necessary by the various factors that can play an important role in modulating effectiveness in real life [37]. Real-world evidence comes from the integration of data from various clinical practices and personal health management with features of integration, personalisation and authenticity [38]. In our study, the daily added salt intake of each household member and the salt consumption-related KAP of the household’s main cook will be collected, which will be used as real-world data from households.

## Methods/Design

### Aim

This study aims to (1) develop an intelligent added salt monitoring system based on real-world study and (2) evaluate the effectiveness of the system in reducing the daily added salt intake of each household member and improving the salt consumption-related KAP of the household’s main cook.

### Design

This pilot study comprises two stages. Each stage achieves one of the objectives described above. Additional file 1 provides the complete Standard Protocol Items: Recommendations for Standard Protocol Items: Recommendations for Interventional Trials (SPIRIT) checklist.

#### Stage 1: Development of intelligent added salt monitoring system (SALTCHECKER)

##### The Development of SALTCHECKER

The entire system will be divided into three parts: front-end sensing, cloud analysis and terminal interaction (Fig. 1).

**Fig. 1 Fig1:**
[figure not shown]
System functional structure diagram

The front-end sensing system is also called the “smart salt checker”. It has a salt container and an electronic salt sensor. The electronic salt sensor is equivalent to a self-designed electronic weighing scale on the base of the salt container, which can weigh the salt in the container, with a weighing range of 0–250 g and a sensitivity of 0.2 g. After the user takes the salt each time, and the container is placed on the base with the lid closed, the processing unit of the electronic salt sensor can immediately detect and record the weight and the time of salt used.

The cloud analysis system can automatically calculate the individual added salt intake of each household member according to the information acquired from the terminal interaction system. The daily added salt intake of each household member will be calculated on the basis of the distribution of staple food consumption of residents in the household. Daily intake estimates of added salt for each household member (g/standard) = (30 days’ intake of added salt by the surveyed household × standard daily number of each member in the household/standard daily number of all people in the household)/30 [39].

The terminal interaction system is a salt-limiting WeChat mini programme; through the programme, basic data can be acquired of the participating household’s main cook and other household members, such as their age, gender, occupation, marital status, education level, height, weight, labour intensity, health status, the number of people per meal and meal ratio per day for members aged>2 years old in their household. Participants with hypertension will also be encouraged to provide data on blood pressure, and the time and tool of blood pressure measurement.

Overall, the SALTCHECKER contains three key features: (1) self-monitoring: to automatically calculate the daily added salt intake of each household member, (2) questionnaires: to investigate the basic demographic information of the household’s main cook and other household members and salt consumption-related KAP of the household’s main cook, (3) personalised reports: through salt-limiting WeChat mini programme, professional nutrition experts in our research group will provide the daily added salt intake of each household member and corresponding healthy salt-using suggestions for specific household members to the household’s main cook.

##### Qualitative interview

During the SALTCHECKER development, a semi-structured in-depth interview will be conducted among the household’s main cook, information technology personnel and nutritionist to determine the content of the system. The selection of candidates for the interview will follow dynamic sampling and information saturation principles until no new useful information can be collected by adding new subjects. Each interview will take around 20 minutes. Interviews will be digitally audio-recorded after obtaining the informed consent of the interviewee. From the interview, the feelings and suggestions for the content of the personalised report, privacy and security protection; system professionalism and functional diversification; health guidance or management category; and other characteristics of the system can be identified. Then, the function of the system can be improved to meet the needs of the residents. Based on the qualitative interview and evidence-based literature, the SALTCHECKER will be finalised and the main content of the personalised report developed.

#### Stage 2: Evaluation of the effectiveness of SALTCHECKER

To evaluate the effectiveness of SALTCHECKER, we will (1) assess the time trend of salt intake change during the study period and (2) compare the individual salt intake of the household member and the salt consumption-related KAP of the household’s main cook between the intervention group and the control group at baseline, 3 and 6 months.

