### Analysis strategy

Statistical analyses will be conducted using SPSS version 22.0 (IBM Corp, Armonk, NY, USA). Descriptive statistics will be calculated for all the variables under examination. The counting data will be described by frequency and percentile, and the metrological data description will use mean, standard deviation and median. The demographic characteristics of the household members (e.g. age, gender, ethnicity, occupation, marital status, education level, height, weight and health status) will be analysed to examine the influencing factors of the household salt monitoring system by using multivariate regression analysis. Linear mixed models, generalized estimating equations (GEE) or t-test will be used to examine the predictors of added salt intake of each household member and salt consumption-related KAP of the household’s main cook and the moderators, mediators of the intervention effects. Correlation analysis will be used to test the link between the score of salt consumption-related KAP and daily added salt intake of each household member. Meanwhile, we will analyse the time trends of the daily added salt intake of each household member during the study period. The level of significance will be set at < 0.05. For the qualitative data analysis, the audio recordings will be transcribed verbatim by trained transcribers. Content analysis of the qualitative information gathered will be done using MAXqda. In addition, if there is enough data acquired about blood pressure, analysis of the impact of the system on blood pressure will be considered.

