## Discussion

This study will be the first to apply IOT technology to monitor and control the added salt intake in Chinese households. We expect to find that the salt consumption-related KAP score will be higher and the daily added salt intake of each household member will be less in the intervention group than in the control group. In the intervention group, we also expect that the time trend of the daily added salt intake of each household member will show an overall downward trend. A stronger reduction is expected in salt over-consumption households, and the strength of the effect is expected to be higher between 3 months and baseline than between 6 months and baseline and between 6 and 3 months due to time effect [16]. We speculate that if the monitoring system is used continuously after 6 months, the salt consumption-related KAP of the household’s main cook will improve continuously or be maintained at a good level, and the daily added salt intake of each household member will decrease continuously or be maintained under the recommended level of the Chinese Nutrition Society (6 g/d) [3]. In addition, the demographic characteristics may be factors that influence the SALTCHECKER effect.

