## Trial status

The project is planned from January 2019 until December 2020. The recruitment phase of this study is scheduled from January 2020 to March 2020. The intelligent household added salt monitoring system will be developed and improved from January 2019 until December 2019. The daily added salt intake of each household member will be monitored from April to September and the salt consumption-related KAP of the household main cook will be investigated in April, July and October 2020. Data analysis and evaluation will be performed after September 2020. The protocol stands at version 3.0 on 10 March 2020.

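### The time trend of salt intake is listed as its own basis for judging effectiveness with no arm contrast, so a drift shared by both arms could be read as an effect of the system

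*Protocol article*

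**What the plan says.** The section on Stage 2 of the protocol article says that effectiveness will be evaluated in two numbered ways. Item (1) is to "assess the time trend of salt intake change during the study period". Item (2) compares individual salt intake and the main cook's KAP "between the intervention group and the control group at baseline, 3 and 6 months". The arm comparison belongs to item (2) only.

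Other sections bear on item (1):

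- **Procedure:** the effect of the system is to be evaluated by changes in intake and KAP; no arm contrast is stated there.
- **Analysis strategy:** "we will analyse the time trends of the daily added salt intake of each household member during the study period". No arm term is named for this. Linear mixed models, GEE or a t-test are named in a separate sentence, for predictors and for moderators and "mediators of the intervention effects".
- **Discussion:** the first expectation is comparative (higher KAP and lower intake than in controls). The trend comes second and for one arm, in a sentence that opens "In the intervention group, we also expect that the time trend of the daily added salt intake"; the direction predicted for it is that it "will show an overall downward trend". The next sentence begins "A stronger reduction is expected in salt over-consumption households" and goes on to compare the strength of the effect between pairs of visits.
- **Trial status:** intake "will be monitored from April to September". Under Intervention, the intervention period is 6 months. Under Control group, controls have the salt checker with its weighing function.

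**The concern.** A trend over time within one arm is not protected by randomisation. Here calendar time and time on the intervention coincide: there is one window from spring to early autumn, and the intervention lasts as long as the window. A seasonal change in cooking, or a reaction to having one's salt weighed, would appear in the intervention arm's trend and could not be told apart from an effect of the reports and education. The Recruitment section accepts this kind of mechanism: it excludes users of tracking devices because such devices may influence behaviour.

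The control arm removes whatever the two arms share, but only if the trend is compared between arms. Item (1) does not say so, and no section gives item (2) precedence. What is at stake is the reading of a mixed result. If the arm comparison is null but intake falls in the intervention arm, the text as written allows the fall to be cited as evidence of effectiveness, even if controls fell equally.

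**Working it through.** The plan gives no figure for a trend, so there is none to reproduce. The sample size does not depend on this point.

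**1. Side-by-side reading.** Item (1) has no arm contrast, the Analysis strategy adds none for the time trends, and the Discussion states the expected direction for one arm. Item (2) has an explicit contrast. A within-arm reading of item (1) is therefore open, though not compelled.

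**2. Within-arm test under no effect.**

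- From the protocol: 300 households per arm; α = 0.05 with critical value 1.96.
- Assumed: household SD 3–4 g/d; baseline to follow-up correlation r of 0.5–0.7; a fall shared by both arms of 0.5 or 1 g/d; one value per household; no dropout.

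SE of the mean change = SD × √(2(1 − r)/300). Chance of a significant fall = Φ(fall/SE − 1.96).

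| SD | r | SE | fall 0.5 g/d | fall 1 g/d |
|---|---|---|---|---|
| 3 | 0.7 | 3 × √(0.6/300) = 0.134 | Φ(1.77) = 96% | >99% |
| 3 | 0.5 | 3 × √(1/300) = 0.173 | Φ(0.93) = 82% | >99% |
| 4 | 0.7 | 4 × √(0.6/300) = 0.179 | Φ(0.84) = 80% | >99% |
| 4 | 0.5 | 4 × √(1/300) = 0.231 | Φ(0.21) = 58% | Φ(2.37) = 99% |

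**3. Simulation in SD units.** No intervention effect, 300 households per arm, 1,500 runs per setting, r = 0.5, 0.7, 0.9.

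| shared fall | significant within-arm fall (r = 0.5 / 0.7 / 0.9) |
|---|---|
| none | 3% / 2% / 2% |
| 0.1 SD | 39% / 60% / 97% |
| 0.2 SD | 94% / 99% / 100% |

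Across all settings the between-arm test of change was significant in 4–6% of runs, because a shared fall cancels. On the assumed SD, 0.5 g/d is 0.5/4 = 0.125 to 0.5/3 = 0.167 SD, between the last two rows.

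**4. Over-consuming households.** Assume normal intake with 38% of households at or below 6 g/d at baseline (the planning proportion under Study sample, applied here to households). The cut-off is then at z = −0.305, where the normal density is 0.381. With no effect and no drift, households above the cut-off fall by (1 − r) × 0.381/0.62 SD, and the gap in change from the other households is (1 − r) × 0.381 × (1/0.62 + 1/0.38) SD.

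| r | fall in over-consumers | gap to the rest |
|---|---|---|
| 0.5 | 0.31 SD | 0.81 SD |
| 0.7 | 0.18 SD | 0.48 SD |
| 0.9 | 0.06 SD | 0.16 SD |

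In the simulation a significantly larger within-arm fall in over-consumers appeared in 100% of runs at r = 0.5 and 0.7 and in 86–88% at r = 0.9. The arm-by-over-consumption interaction was significant in 5–6%.

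**The case against.** Item (1) is not expressly limited to one arm. Both arms are weighed over the same period, so the trend can be compared between them. The Discussion puts the comparison with controls first, and its statement about the intervention arm is a prediction rather than a decision rule. Item (2) would show whether controls fell as well. Model terms are often left to an analysis plan, which is not shown. All this is fair, and it limits the point to one of wording. It does not remove it: the article itself states how effectiveness will be judged, and that statement lists the trend apart from the arm comparison.

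The drift figures are assumptions. The documents give no size or direction for season or reactivity, and a seasonal rise would hide a true fall rather than create a false one. That stands; the percentages show sensitivity and are not a forecast.

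Three stronger readings are tempting and are not supported:

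- *Larger falls in over-consuming households are a criterion of effectiveness.* They are neither in the Stage 2 list nor among the primary outcomes. They appear only as an expectation in the Discussion, and the planned moderator analysis could already test them between arms.
- *Regression to the mean would produce the overall trend.* Households are not selected on intake, so it does not move the arm mean; it bears only on the contrast by baseline intake. The intake formula averages over 30 days, so the correlation may be high and the artefact small, though at 0.9 the within-arm contrast was still usually significant. A high correlation also makes a shared drift easier to detect, so it does not help the trend reading.
- *The trial's effectiveness result is undermined.* The randomised comparison in item (2) is unaffected.

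**Conclusion.** The point holds as one of wording, and it is worth correcting. As written, a downward trend within the intervention arm could count as evidence of effectiveness although season or reactivity to weighing could cause it. With an assumed SD of 3–4 g/d, correlation of 0.5–0.7 and 300 households, a shared fall of 0.5 g/d would make that trend significant in 58–96% of trials with no effect, and 1 g/d in about 99% or more; a between-arm test stays near its nominal 5%. SD, correlation and drift are all assumptions. The matter of over-consuming households is a secondary clarification: a within-arm comparison would be open to regression to the mean, by an amount that depends on an unknown correlation (a fall of 0.31 SD at 0.5, 0.06 SD at 0.9).

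**What to change.** - In the Stage 2 section and the Analysis strategy, state that time-trend evidence of effectiveness is the arm-by-time contrast in the planned mixed model or GEE, and that within-arm trends are descriptive only.
- If the Discussion's expectation about over-consuming households is to be examined, say that it will be tested within the planned moderator analysis as an arm-by-baseline-intake interaction, with baseline intake kept continuous, and not by change within high-baseline households of one arm.

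The cost is a few sentences. The control arm, the repeated measurements and the models are already planned, and neither the sample size nor the data collection changes.

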### Procedure

A baseline survey will obtain the household demographic information and the salt consumption-related KAP of the household’s main cook. In the test period, the household’s main cook in the intervention group will use the smart salt checker and the salt-limiting WeChat mini programme, while the household’s main cook in the control group will use the smart salt checker with only the weighing function. The data of the daily added salt intake of each household member will be automatically calculated using SALTCHECKER. And the salt consumption-related KAP of the household’s main cook will be assessed at the beginning of the test (i.e. at baseline), the third month and the sixth month after the test. Finally, the effect of the household added salt monitoring system will be evaluated by changes in daily added salt intake of each household member and the salt consumption-related KAP of the household’s main cook. The technological roadmap is shown in Fig. 2.

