#### Randomization and blinding

After the baseline survey, 600 participating households’ main cooks will be randomly divided following a 1:1 ratio into the intervention group and the control group by the household demographic information, with 300 households in each group. The study coordinator will be responsible for the randomization and verification of the computer-generated intervention assignment with a randomization table. All the investigators, except for the study coordinator, will be blinded. The participants will be blinded and instructed not to inform the other participants of the treatment they receive.

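### The arm contrast for the two primary outcomes is described in inconsistent ways, includes a baseline comparison that cannot inform effectiveness, and is never fixed as baseline-adjusted

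*Protocol article*

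**What the plan says.** Both primary outcomes, daily added salt intake of each household member and the main cook's KAP, are assessed at baseline, 3 and 6 months (Primary outcomes). The arm contrast is described in several places:

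- **Stage 2.** The first element of the effectiveness evaluation is to "assess the time trend of salt intake change during the study period". The second is to compare salt intake and KAP "between the intervention group and the control group at baseline, 3 and 6 months". Baseline stands in that list on the same footing as the two follow-up visits.
- **Procedure.** Here "the effect of the household added salt monitoring system will be evaluated by changes in daily added salt intake of each household member" and in the cook's KAP.
- **Analysis strategy.** "Linear mixed models, generalized estimating equations (GEE) or t-test will be used to examine the predictors of added salt intake of each household member" and KAP, and also moderators and mediators. The choice among the three methods is left open, and the role of the baseline value is not stated.
- **Discussion.** The expectation is that "the strength of the effect is expected to be higher between 3 months and baseline than between 6 months and baseline", so the authors have contrasts with baseline in mind.

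On timing, Randomization and blinding places allocation after the baseline survey ("After the baseline survey, 600 participating" main cooks are then divided 1:1), "with 300 households in each group".

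**The concern.** Two things are wrong in what is written.

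First, the baseline arm comparison is listed among the comparisons that evaluate effectiveness. Where the value was measured before allocation, any arm difference in it arose by chance. It belongs in a table of baseline characteristics, not in the evaluation of the effect.

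Second, a difference in levels at a visit and a difference in changes are different estimators of the same effect, and the protocol names both for the same primary outcomes. They respond differently to chance imbalance. If the arms differ at baseline by D, and the standard deviation is the same at both times, a follow-up-only contrast is expected to shift by rD and a change-score contrast by −(1−r)D. The two can therefore give visibly different answers from one data set, and the methods sentence does not settle which is meant.

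At stake are precision on both primary outcomes and a choice among contrasts that could be made after the data are seen. Validity is not at stake, because randomisation protects each of these contrasts on average.

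**Working it through.** **Plan's own figure.** The only related calculation is the sample size: (1.96 + 1.28)² × 2 × 0.42 × 0.58 / 0.08² = 799.1, which reproduces the stated 799. It concerns a proportion at or below 6 g/d and contains no baseline–follow-up correlation, so it neither supports nor weakens this point.

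**Inputs.** There are 300 households, and so 300 cooks, per arm (Randomization and blinding), and α is 0.05 with 1.96 (Study sample). The protocol gives neither r nor a standard deviation. I assume r = 0.3 to 0.8, equal variance at baseline and follow-up, and one independent unit per household. That fits KAP directly. For salt intake it ignores the clustering of members within households.

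**Variance of the arm contrast at one follow-up visit, relative to follow-up only (= 1)**

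- Change score: 2(1 − r)
- Adjusted for baseline: 1 − r²
- Adjusted relative to change score: (1 − r²) / [2(1 − r)] = (1 + r)/2

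| r | Change score | Adjusted | Adjusted ÷ change score |
|---|---|---|---|
| 0.3 | 1.40 | 0.91 | 0.65 |
| 0.5 | 1.00 | 0.75 | 0.75 |
| 0.7 | 0.60 | 0.51 | 0.85 |
| 0.8 | 0.40 | 0.36 | 0.90 |

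Adjustment beats both alternatives for every r strictly between 0 and 1. Below r = 0.5 a change score is less precise than ignoring baseline altogether.

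**In terms of power.** Take the difference that a follow-up-only comparison detects with 80% power at 300 per arm: √(2/300) × (1.960 + 0.842) = 0.229 SD.

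| r | Follow-up only | Change score | Adjusted |
|---|---|---|---|
| 0.3 | 80.0% | 65.8% | 83.6% |
| 0.5 | 80.0% | 80.0% | 89.9% |
| 0.7 | 80.0% | 95.1% | 97.5% |
| 0.8 | 80.0% | 99.3% | 99.7% |

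**Is there a baseline value before randomisation?** For KAP, yes: the Procedure section puts it in the baseline survey, and allocation comes afterwards. For salt intake the sections do not agree:

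- The heading Baseline survey includes daily added salt intake, but the Procedure section describes that survey as covering demographics and KAP only.
- The intake formula under The Development of SALTCHECKER needs 30 days of household salt use.
- The Intervention group section has the device installed in the intervention period, which lasts 6 months.
- Trial status has salt monitored from April to September, which is 6 calendar months. A 30-day baseline window followed by 6 months of intervention needs about 7.

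So a salt value labelled baseline could come from the first month of intervention.

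**The case against.** The strongest reply is that most of a harsher criticism would be inference, and that is right on several counts.

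- **A reader might infer that the baseline value goes unused.** The document does not support this. The Procedure section evaluates changes, Stage 2 lists the time trend of change, and the Discussion frames the expected effects against baseline.
- **A reader might infer that a significance test at baseline is planned.** Stage 2 only says compare. No section announces such a test, and a descriptive table would fit the word. What stands is that this comparison is placed within the effectiveness evaluation.
- **A reader might infer separate t-tests at each visit.** The methods sentence attaches its three methods to predictors, moderators and mediators, and two of the three can take all visits together. What stands is that the t-test remains an allowed option. Moreover, a mixed model with free arm means at baseline, read as change from baseline, gives the change-score contrast when data are complete.
- **A reader might quote a power gain from 71% to 83–94%.** That figure takes 38% against 46% as 0.205 SD on a normal scale, assumes r = 0.5 to 0.7, and compares only with a follow-up-only analysis. Against a change score at r = 0.7 the gain is from about 90% to 94%: Φ(0.205 × √(150/0.60) − 1.96) against Φ(0.205 × √(150/0.51) − 1.96). The 0.205 also derives from a salt proportion and says nothing about KAP.

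It can also be said that a condensed article may leave model terms to an analysis plan. I accept that an unstated covariate would not be a finding by itself. The point rests on what is stated: contrasts that disagree, one of which cannot bear on effectiveness.

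**Conclusion.** The point holds in a limited form. The protocol describes the arm contrast for its two primary outcomes inconsistently and counts a baseline arm comparison towards effectiveness although allocation follows the baseline survey. The two contrasts it describes, levels and changes, are both less precise than a baseline-adjusted one.

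The size depends on r, which the protocol does not give. Over an assumed 0.3 to 0.8, adjustment cuts the variance by 9% to 64% against follow-up only and by 35% to 10% against a change score. The gain is therefore modest if changes were intended and r is high, and large if levels were intended and r is high. These figures assume equal variances and independent units.

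The conclusion applies directly to KAP. For salt intake it is conditional on a value obtained before randomisation. Adjusting for a value measured under the intervention could bias the effect. The change is worth making before analysis, but its absence would not invalidate the trial.

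**What to change.** 1. In Stage 2, take baseline out of the effectiveness comparisons and report baseline values by arm descriptively, without a test.
2. State one linear mixed model per primary outcome: 3- and 6-month values on arm, visit, arm-by-visit and the pre-randomisation baseline value as covariate, accounting for household. Give the arm difference at each visit from that model. Which visit should be primary is a separate question, not raised here.
3. Align Stage 2, Procedure and Analysis strategy so that all three name this contrast, and drop the t-test as an alternative for it.
4. For salt intake, reconcile The Development of SALTCHECKER, Procedure, Baseline survey, Randomization and blinding, Intervention group and Trial status on when the baseline value is obtained. Use it as a covariate only if that is before randomisation. Otherwise fit the same model for salt without it.

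For KAP the cost is wording only: the baseline score is already planned and linear mixed models are already listed. For salt intake the authors must also settle the measurement window, which may affect the calendar.
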